### Recruitment

Possible participants are approached through ads on social networks. Those interested in using the application are asked to access the study’s website – www.binedispus.ro, read the information package, and follow the online standard recruitment procedure. They are subsequently contacted by phone, at which point the enrollment procedure is described and the short screening phone interview takes place.

### Assignment to study group

The participants are randomly assigned to one of the three trial arms, using the software Randomizer.org. Randomization is performed by a research assistant using a simple (unrestricted) randomization sequence that assigns three unique numbers per participant; the number assigned is either 1, 2, or 3 according to the number of the experimental condition. To conceal the allocation mechanism, the same research assistant will monitor the assessments and allow access to the application for the participants in the wait-list control group after 6 weeks. The principal investigator and the statisticians running the data analysis will remain blinded to the study condition until the completion of the study.

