#### Eligibility criteria

##### Inclusion criteria

Healthy Romanian-speaking adults (18 years or older), with access to a computer, a smartphone (Android or iOS), and the Internet are included in the study. The Structured Clinical Interview for *Diagnostic and Statistical Manual of Mental Disorders, Fourth Edition, Text Revision* (DSM-IV) (SCID) [33], specifically, the Overview Module will be used to determine the general clinical status of the participants. A clinical psychologist will conduct a short interview aimed to screen for exclusion criteria (see below). Information on drug use and physical and psychological treatment status will be collected. In addition, to be included in the study, participants should report a Patient Health Questionnaire-9 (PHQ-9) score above 9, but no greater than 16.

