#### Participant timeline

Potential participants will be assessed for eligibility through an initial assessment of depressive symptoms. The initial assessment phase consists of administration of the PHQ-9 and a short phone screening interview. Applicants who do not meet the inclusion criteria are informed via e-mail. They are given a summary score and interpretation for their PHQ-9 score and they are encouraged to discuss their problems with a professional, if necessary. Information on how to reach one – a clinical psychologist or a psychotherapist – is also provided.

After the initial assessment, the participants meeting the inclusion criteria will be randomly assigned to one of the three conditions: (1) active intervention condition – mHealth CBT (group 1), (2) the PI (group 2), or (3) the delayed-intervention condition (WL) (group 3) (see flow diagram in Fig. 4). Subsequent assessments consist of all the instruments presented in the “Outcome measures” section. Figure 5 shows the schedule of enrollment, interventions, and assessments which accords with the SPIRIT figure.

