### Data collection, management, and analyses

#### Data collection methods

The initial assessment data are collected via the project website. Afterwards, a research assistant conducts telephone-screening interviews with potential participants to determine eligibility, and provides clinical screening reports. All subsequent assessment data are collected within the application, in the Evaluation section, and transferred to our servers using an encrypted, secure (https) industry-standard transfer protocol.

As far as participant retention and follow-up completion are concerned, the therapist check-in component of both the active and placebo interventions will play an important role. Besides being reminded of the specific assessment that needs to be completed after each intervention module, through the Messages section, the participants will also be encouraged by their assigned therapist to complete the assessments. Also, the therapist informs them that the weekly completion of the mood questionnaires allows the app to create a personalized profile of their mood, along with individualized visual feedback on their emotional state. Moreover, they are rewarded with more Energy after completing every assessment. Finally, for the follow-up assessments, the participants will receive new messages reminding them that free use of the app was possible because of a research grant, and thus data collection is essential. Additionally, participants are informed that they can attend an online psychological assessment with a clinical psychologist, based on the completion of follow-up questionnaires, if they wish to do so.

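### The arrangement offered as allocation concealment does not conceal, and the description of the randomisation sequence contradicts itself

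*Protocol article*

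**What the plan says.** Assignment to study group describes who randomises, how, and what is meant to protect the allocation.

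- **Who:** "Randomization is performed by a research assistant", using Randomizer.org.
- **How:** by a "simple (unrestricted) randomization sequence that assigns three unique numbers per participant". The sentence goes on: "the number assigned is either 1, 2, or 3 according to the number of the experimental condition".
- **Concealment:** "To conceal the allocation mechanism, the same research assistant will monitor the assessments and allow access to the application". The sentence then limits that access to wait-list participants after 6 weeks.
- **Blinding:** "The principal investigator and the statisticians running the data analysis will remain blinded to the study condition". No other staff are said to be blinded.

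Two sections describe the screening interview. Inclusion criteria says: "A clinical psychologist will conduct a short interview aimed to screen for exclusion criteria". Data collection methods says: "a research assistant conducts telephone-screening interviews with potential participants to determine eligibility". Participant timeline gives the order: "After the initial assessment, the participants meeting the inclusion criteria will be randomly assigned".

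**The concern.** Concealment means that the person who decides whether someone enters the trial cannot know or guess the next arm. The article states a measure under that name, and the measure does something else. It also describes the sequence in terms that do not fit together. These are things stated wrongly, not details that a journal article leaves to a fuller document.

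Entry depends partly on judgement. The PHQ-9 limits are numerical, but the interview also covers substance abuse, psychotic symptoms and serious health problems (Exclusion criteria). A screener who could foresee the arm would have room to influence who enters it. The trial exists to separate a genuine effect from a digital placebo effect (Objectives), and selection into arms would bias that comparison. Adjusting for measured baseline values could not fully remove such a bias.

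**Working it through.** The plan gives no figure of its own on this point. The check compares the statements and then works out how far the possible readings of the sequence differ.

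**1. Does the stated measure conceal?** The assistant has three stated duties: randomising, monitoring assessments, and opening wait-list access at 6 weeks. The last two follow allocation. They neither reveal nor hide an upcoming assignment. Concealment depends on who holds the sequence and who can see it before a participant is accepted. On that, the section says only that the assistant performs the randomisation.

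**2. What is the sequence?** The text makes three statements: unrestricted; three unique numbers per participant; the number assigned is 1, 2 or 3.

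- *Simple randomisation.* Each person gets one independent draw, and a best guess is right with probability 1/3 = 33%. The reference to three unique numbers then has no role.
- *Sets of three across successive participants.* Three unique numbers from 1 to 3 form a permutation, which is a block of 3 and therefore restricted. Someone who knows all earlier allocations guesses the three places with probabilities 1/3, 1/2 and 1. The average is (0.333 + 0.500 + 1.000)/3 = 0.611, and every third allocation is certain.
- *Three numbers for one person, taken literally.* No rule says which of the three is used. If the first were used, it would be uniform on 1 to 3 and independent between people, which is simple randomisation again. The text does not say so.

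The three statements therefore do not fit together without a rule that the text does not give.

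**3. How much does simple randomisation cost at the target?** Inputs are 220 participants (Sample size) and three equal arms (Trial design gives a 1 in 3 chance of placebo).

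- SD of an arm size = √(220 × 1/3 × 2/3) = √48.9 = 7.0.
- Simulated over 400,000 allocations, the largest and smallest arms differ by at least 10 with probability 0.71 and by at least 20 with probability 0.24.
- The smallest arm has 59 or fewer with probability about 7%.
- Relative to equal arms, the variance of a two-arm contrast rises by 0.9% on average and by 9.6% at the 95th percentile.

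The loss of precision is small. Sets of three would give 74/73/73.

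**4. Who screens?** One section names a clinical psychologist and the other a research assistant. Neither says whether this is the assistant who randomises, and nothing states that the two roles are kept apart.

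**5. When was the sequence made?** Trial status dates the start of recruitment to 15 February 2017 and says randomisation was performed that day. The abstract's registration entry dates the first enrolment to 17 February. Participant timeline puts assignment after the initial assessment. One explanation is that a list existed before anyone was enrolled, in which case who could see it matters. The article does not settle this.

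**The case against.** The strongest reply is that the route to bias is inferred. It needs the person deciding eligibility to see the sequence. Assignment to study group refers to the same assistant only for randomising, monitoring and wait-list access, while Data collection methods refers to an unspecified research assistant. A reader might infer that one person screens, randomises and grants access to every arm. The article supports neither the shared identity nor access beyond the wait-list arm. It also reports no breach. All of this stands and limits the conclusion.

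A charitable reading is that the concealment sentence is a mislabelled blinding measure, confining knowledge of the arm to one assistant so that the principal investigator and statisticians stay blind. That may be the intention. It would still leave concealment unaddressed under a sentence that claims it.

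The two sections on screening may also be compatible, since a research assistant can be a clinical psychologist. That is possible, and it is why they need reconciling rather than being counted as proof of a conflict.

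Finally, a reader might conclude that the trial uses blocks of 3 and that its allocations are predictable. The text does say unrestricted, and if that holds nothing can be predicted. The 61% belongs to one interpretation and requires knowledge of past allocations. Nor is imbalance a fault here: simple randomisation at 220 is legitimate, and its cost in precision is small.

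**Conclusion.** The point holds in a limited form. The measure presented as concealment does not conceal, and the sequence description is internally inconsistent. Both follow from the text of one section. The uncertainty about who screens adds to the concern but does not establish that the screener could see the sequence.

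The possible size depends on the reading: best-guess accuracy is 33% if the scheme is simple and 61% if sets of three were used and earlier allocations were known. Neither figure measures bias in the depression outcome, which the document gives no means to estimate. The conclusion is that the procedure as described does not secure concealment, not that concealment failed. It should be corrected.

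**What to change.** For participants not yet randomised:

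- Let the existing study server hold the sequence and release each arm only after eligibility and baseline are locked.
- Have eligibility decided by someone with no access to the sequence or to past allocations. This needs care if a clinical psychologist screens: under Therapist check-in, three clinical psychologists handle all clinical contact with the two app arms, so any of them would learn part of the allocation history.
- Keep simple randomisation, or state the restricted scheme actually used. A move to blocks is not needed and would make allocation more predictable.

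In the text:

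- Delete the sentence that presents the assistant's combined duties as concealment, and describe the true method.
- Reconcile Inclusion criteria with Data collection methods on who conducts the screening interview.
- Because recruitment has begun, report how the allocations already made were generated, when, and who could see them.

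The cost is a small server script and revised wording. Allocations already made cannot be concealed after the fact, so for them the remedy is disclosure only.

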### Data collection, management, and analyses

#### Data collection methods

The initial assessment data are collected via the project website. Afterwards, a research assistant conducts telephone-screening interviews with potential participants to determine eligibility, and provides clinical screening reports. All subsequent assessment data are collected within the application, in the Evaluation section, and transferred to our servers using an encrypted, secure (https) industry-standard transfer protocol.

As far as participant retention and follow-up completion are concerned, the therapist check-in component of both the active and placebo interventions will play an important role. Besides being reminded of the specific assessment that needs to be completed after each intervention module, through the Messages section, the participants will also be encouraged by their assigned therapist to complete the assessments. Also, the therapist informs them that the weekly completion of the mood questionnaires allows the app to create a personalized profile of their mood, along with individualized visual feedback on their emotional state. Moreover, they are rewarded with more Energy after completing every assessment. Finally, for the follow-up assessments, the participants will receive new messages reminding them that free use of the app was possible because of a research grant, and thus data collection is essential. Additionally, participants are informed that they can attend an online psychological assessment with a clinical psychologist, based on the completion of follow-up questionnaires, if they wish to do so.

#### Statistical methods

Post-treatment analyses involve an intent-to-treat (ITT) design with the first available data after the baseline carried forward.

Improvement in the primary outcomes measures scores within and between the groups will be examined using mixed-effects linear regression analyses with a random intercept and slope over time (four assessments: baseline, mid-intervention, post intervention, and follow-up) and fixed effects for intervention assignment. The main analysis will compare groups (active intervention, PI, and WL) in terms of the level of depressive symptoms. When the analysis of secondary/other outcomes is performed, the error probability will be adjusted according to the number of group comparisons performed.

App usage data and user activity will be examined by comparing, for example, the participants’ self-reported activity with their actual app usage as recorded by our software. This will inform us about any obstacles to user adherence to the protocol, as well as specific usage patterns.

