#### Measures of primary, secondary, and other outcomes

The following measures have been adapted into Romanian and successfully used in two previous trials testing another version of the app, and they have shown adequate psychometric properties [36].

The level of depressive symptomatology is assessed with the Center for Epidemiologic Studies Depression Scale–Revised (CESD-R) [37, 38]. The CESD-R is a 20-item self-report instrument, which measures symptoms of depression in nine different groups: sadness (dysphoria), loss of interest (anhedonia), appetite, sleep, thinking/concentration, guilt (worthlessness), tiredness (fatigue), movement (agitation), and suicidal ideation. Participants rate each item on a 5-point Likert scale, from 0 (not at all or less than 1 day) to 4 (nearly every day for 2 weeks) to indicate how they felt or behaved during the last week or so. The total CESD-R score is calculated as a sum of responses to all 20 questions. The CESD-R exhibited good psychometric properties, including high internal consistency, strong factor loadings, and theoretically consistent convergent and divergent validity with anxiety, schizotypy, and positive and negative affect [39].

*The Positive and Negative Affect Scale* (PANAS) [40] is a 20-item self-report questionnaire designed to assess mood. It consists of 10 items that address positive affect (PA) and 10 items that address negative affect (NA). Participants rate each item on a 5-point Likert scale, from 1 (very slightly/not at all) to 5 (extremely) to indicate how they felt during the indicated time frame. The PANAS can be used to assess mood on various time scales by altering the instructions. For the purposes of this study we have used a 2-week time frame. The validity and internal consistency of the PANAS are good, with test-retest reliability being the highest for the “general” temporal instruction. The PANAS has been used previously on the Romanian population and was found to have adequate psychometric properties [41, 42].

*Satisfaction with Life* (SWL) [43] is a five-item scale designed to measure global cognitive judgments of one’s life satisfaction. Participants rate each of the five items using a 7-point scale that ranges from 7 (strongly agree) to 1 (strongly disagree). The SWL has been shown to be a valid and reliable measure of life satisfaction which can be used with a wide range of age groups [44, 45].

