**Fig. 5 Fig5:**
[figure not shown]
Schedule of enrolment, interventions, and assessments

The participants in the active intervention and active placebo conditions are assessed at preintervention (time 1 – baseline), at mid-intervention (time 2 – 3 weeks after baseline), at post intervention (time 3 – 6 weeks after baseline), and at 3 months post intervention (time 4). The participants in the delayed-intervention condition are assessed before the waiting period (time 1 – baseline), at mid-waiting period (time 2 – 3 weeks after baseline), and at post waiting period (time 3 – 6 weeks after baseline).

Participants assigned to the active intervention condition will be given access to the online application along with explicit instructions regarding the use of all its sections. Participants will be given 6 weeks to complete the intervention, during which time weekly messages will be sent out to them. Messages include regular assignments designed for a complete and thorough use of the application’s courses and exercises, and encourage the review of materials whenever possible. However, participants are free to use the application at their own pace.

Similarly, the participants in the active placebo condition will be given access to a sham version of the app. During the 6-week intervention period they will be exposed to the same amount of online (i.e., in-app messages) and therapist communication as the active intervention participants.

After each week, participants’ app use is evaluated (see the Application Use Scale described above). Similarly, after each week of using the app, the participants are required to complete the CESD-R to monitor their depressive symptomatology and provide individualized in-app feedback on their emotional state.

The participants in the delayed-intervention condition are placed on a wait-list for 6 weeks, after which time they are given full access to the app.

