#### Sample size

A total of 165 participants with moderate depressive symptomatology was estimated. This is based on previous studies on the efficacy of mobile phone applications for depression, which reported small to moderate between-group effect sizes [19, 24]. An a priori sample size calculation was conducted with G*Power 3.1.9.2 [58, 59] for analysis of variance (ANOVA) (repeated measures, between factors), assuming an alpha level of 0.05, a statistical power of 0.80, and a small to medium effect size (*f* = 0.2). Since the current protocol has a therapist check-in component, a sample size recruitment target of *N* = 220 was set to allow for sample attrition, thus estimating a dropout rate of approximately 30%.

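### The intention-to-treat rule fills missing outcomes with the earliest post-baseline score, which shrinks the week-6 difference and can distort it when dropout is unequal

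*Protocol article*

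**What the plan says.** The missing-data rule is one sentence in the protocol article, section Statistical methods: "Post-treatment analyses involve an intent-to-treat (ITT) design with the first available data after the baseline carried forward". Nothing elsewhere in the article qualifies it. The next paragraph of that section plans "mixed-effects linear regression analyses with a random intercept and slope over time (four assessments: baseline, mid-intervention, post intervention, and follow-up").

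The primary outcome is depressive symptoms: "The level of depressive symptomatology is assessed with the Center for Epidemiologic Studies Depression Scale–Revised (CESD-R").

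The section Participant timeline schedules the active and placebo arms "at mid-intervention (time 2 – 3 weeks after baseline), at post intervention (time 3 – 6 weeks after baseline"), with a further assessment three months after the intervention. The wait-list is assessed "at mid-waiting period (time 2 – 3 weeks after baseline") and again at week 6. The same section adds, for app users, that "after each week of using the app, the participants are required to complete the CESD-R".

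The Sample size section expects a dropout rate of about 30%.

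**The concern.** The earliest post-baseline score is generally a poor stand-in for a missing week-6 score. It is taken when the intervention has had least time to act, and using it discards any later score the participant gave. If the weekly CESD-R counts, someone who leaves after week 5 would be represented by week 1.

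Three things are at stake for the active-versus-placebo comparison, which the Objectives section names as the aim:

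- With equal dropout, the treatment difference is pulled towards zero.
- With unequal dropout, a difference can be created or hidden, because improvement is erased in proportion to each arm's missingness.
- Filled values enter as if observed, so precision is overstated.

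The rule is also unnecessary. The planned mixed model can use incomplete series directly, and the text does not say how carried values would enter it.

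**Working it through.** **The plan's own figure.** The sample size does not depend on this rule. For completeness, the stated 165 reproduces from the section's settings ("assuming an alpha level of 0.05, a statistical power of 0.80, and a small to medium effect size", *f* = 0.2), taking three groups and assuming three measurements with a correlation of 0.5, neither of which is stated. The noncentrality is 0.04 × 165 × 3 / (1 + 2 × 0.5) = 9.9 on 2 and 162 degrees of freedom, and power is 0.804.

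**Inputs.**

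- Missing at week 6, *d*: 0.30 from the Sample size section. I also use 0.25, which is what 165 out of 220 implies (1 − 165/220).
- Carried visit: week 3 (main assessments only) or week 1 (weekly CESD-R counted).
- Share of the week-6 change reached at the carried visit, *w*: the documents give no trajectory, so a linear course is assumed. This gives *w* = 3/6 for week 3 and 1/6 for week 1.
- Mean changes of −8 and −6 points, and 40% versus 20% missing: illustrative assumptions.

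**Formula.** If an arm's true mean change at week 6 is *C*, the expected change after filling is *C* × [1 − *d*(1 − *w*)]. With the same *d* and *w* in both arms, the difference shrinks by the same factor.

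**Equal missingness, share of the true difference kept.**

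- *d* = 0.30: week 3 gives 1 − 0.30 × 1/2 = 0.85; week 1 gives 1 − 0.30 × 5/6 = 0.75.
- *d* = 0.25: week 3 gives 0.875; week 1 gives 0.79.

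**In points (active minus placebo; negative favours active).**

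| Scenario | True | Week 3 carried | Week 1 carried |
|---|---|---|---|
| −8 vs −6; 30% missing in both | −2 | −6.8 + 5.1 = −1.7 | −6.0 + 4.5 = −1.5 |
| −8 vs −6; 40% vs 20% missing | −2 | −6.4 + 5.4 = −1.0 | −5.33 + 5.00 = −0.33 |
| −6 vs −6; 40% vs 20% missing | 0 | −4.8 + 5.4 = +0.6 | −4.0 + 5.0 = +1.0 |

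If the missingness is swapped between arms, the sign of the last row reverses.

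**Simulation check** (73 per arm, 4,000 replicates, random intercepts and slopes, dropout unrelated to outcome). A true difference of 0.40 SD with 30% missing in both arms became 0.342 (week 3) and 0.302 (week 1). With no true difference, a common 1 SD improvement and 30% versus 20% missing, the spurious difference was about 0.05 SD (week 3) to 0.085 SD (week 1) against the arm with more dropout.

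**Power.** For an illustrative pairwise difference of 0.4 SD (2 × *f*) at 73 per arm, normal-approximation power falls from 0.68 to 0.54 (0.34 SD) or 0.44 (0.30 SD). This counts the attenuation alone.

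**If the wording is a slip for last observation carried forward.** With the last observed week spread evenly over weeks 1 to 5, average *w* is (1 + 2 + 3 + 4 + 5)/(5 × 6) = 0.5, which keeps 85% at 30% missing. The simulation gave 0.342.

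**The case against.** The strongest reply is that the analysis is defined over four assessments, the first post-baseline one being week 3 in every arm, and that the weekly CESD-R is described for monitoring and in-app feedback. This is a fair reading. On it, the week-3 column applies and the loss is about 15% at 30% missing. The week-1 column applies only if weekly scores count as available data, which the sentence neither says nor excludes.

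The size also depends on the course and on who drops out. If the between-group contrast among those with missing data were the same at the carried visit as at week 6, there would be no bias. The 40% versus 20% split is not in the protocol, and both app arms receive the same messages and therapist contact. The figures concern the week-6 mean difference; the effect on a fitted slope depends on how carried values enter the model.

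Several stronger readings are tempting but not supported:

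- *All week-6 outcomes are replaced.* On the natural reading only missing values are filled.
- *The carried week certainly differs between the app arms and the wait-list.* Participant timeline gives the wait-list only weeks 3 and 6 after baseline. But Monitoring study implementation speaks of weekly CESD-R review for every participant, by an assigned clinician, while Therapist check-in describes clinical contact only for the active and placebo arms. The asymmetry is possible, not established.
- *The analysis is not intention-to-treat because some participants have nothing to carry.* Baseline is one of the modelled assessments, so they can remain through that record.
- *The rule contradicts the mixed model.* A mixed model can be fitted to filled data. The text leaves the combination unclear, which is not a contradiction.
- *The standard error is understated by 16%.* That ratio, √(51/73) = 0.84, treats carried scores as holding no information. They are real scores from the same people, so the amount is not fixed by the documents.

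**Conclusion.** The stated rule is wrong as written and should be corrected before analysis. This is an explicit rule that touches the primary outcome, so it cannot be put down to detail left to an analysis plan.

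Under a linear course with 30% missing in each arm, it removes about 15% of the true week-6 difference if week 3 is carried and about 25% if week 1 is carried. At 25% missing the losses are about 12.5% and 21%. With unequal dropout it can produce a difference where none exists: 0.6 to 1.0 points in the 6-point, 40% versus 20% illustration. The direction follows the dropout imbalance. Precision is overstated by an unknown amount.

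The direction of the attenuation rests on improvement continuing after the carried visit. The sizes rest on the assumed linear course, on the assumed missingness by arm, and on dropouts following the same mean course as completers.

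**What to change.** Delete the carry-forward sentence. State instead that all randomised participants are analysed in their assigned arm, with the planned model ("mixed-effects linear regression analyses with a random intercept and slope over time") fitted by likelihood to all observed CESD-R assessments, without filling missing values, under a stated missing-at-random assumption. Participants with only a baseline score stay in through that record. This avoids building in the attenuation shown above if missingness is at random; it does not protect against missingness that depends on unobserved scores.

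Two additions are optional. One is a sensitivity analysis for data missing not at random, such as delta-adjusted or reference-based multiple imputation. The other is use of the weekly CESD-R scores in the active-versus-placebo comparison, which would be a different model from the stated four-assessment one.

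The cost is analysis wording only. No new data are needed and the sample size calculation is unaffected.

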#### The wait-list control group

Participants in the delayed-intervention group are placed on a wait-list for 6 weeks; then they are given full access to the application.

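### One mixed model over four assessments covers all three arms, but the wait-list has only three; if groups are compared on slopes and app users plateau, app versus wait-list is understated

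*Protocol article*

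**What the plan says.** Statistical methods in the Protocol article states the purpose of the model as follows: "Improvement in the primary outcomes measures scores within and between the groups will be examined". The tool is "mixed-effects linear regression analyses with a random intercept and slope over time (four assessments: baseline, mid-intervention, post intervention, and follow-up"), with fixed effects for intervention assignment. The next sentence reads "The main analysis will compare groups (active intervention, PI, and WL) in terms of the level of depressive symptoms". So one model, four assessments and three arms are fixed together.

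The text on the assessment schedule (Participant timeline, after Fig. 5) differs by arm. App and placebo participants are assessed at baseline, week 3 and week 6, "and at 3 months post intervention (time 4"). For the wait-list it says "The participants in the delayed-intervention condition are assessed before the waiting period (time 1 – baseline"), then at week 3, "and at post waiting period (time 3 – 6 weeks after baseline"). No time 4 is listed for that arm. The section on the wait-list control group explains why none could serve as an untreated comparison: "Participants in the delayed-intervention group are placed on a wait-list for 6 weeks; then they are given full access to the application".

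No section restricts wait-list comparisons to the three shared visits, names week 6 as the contrast, or states a group-by-time term.

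**The concern.** A straight line fitted through follow-up describes about 19 weeks in the app and placebo arms but only 6 weeks in the wait-list arm. If improvement between groups is read as a difference in these slopes, the two sides of the wait-list contrast measure different periods. The programme runs for 6 weeks, and the Background notes that gains from computerised CBT have been reported not to last, so levelling off after week 6 is plausible. It would flatten the app slope and leave the wait-list slope as it is. A real benefit over no treatment at week 6 would then look smaller and be missed more often. The wait-list contrast is part of the main analysis, so this would reach a main result.

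The carry-forward rule in the same section adds a smaller risk. Nothing prevents it from being used to fill a wait-list time 4 that was never scheduled.

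**Working it through.** **The plan's own figure.** Sample size says "A total of 165 participants with moderate depressive symptomatology was estimated", for repeated-measures ANOVA, between factors, f = 0.2, alpha 0.05, power 0.80. The number of measurements m and the correlation rho are not stated. With noncentrality f² × N × m / (1 + (m-1) × rho) and degrees of freedom 2 and N-3:

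- m = 3, rho = 0.5: 0.04 × 165 × 3 / 2 = 9.9, power 0.804. N = 165 is reproduced.
- m = 4, rho = 0.5 gives 156; m = 4, rho = 0.55 gives 165.

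The figure therefore does not settle how many visits were planned for. Below, 165/3 = 55 per arm (equal arms assumed).

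**Assumed inputs (not in the document).** Mean change in SD at times 1-4: app 0, -0.3, -0.6, -0.6; wait-list 0, -0.1, -0.2, none. The true week-6 difference is 0.40 SD. Follow-up is taken as week 6 + 13 = 19. Residual variance is 0.4-0.5, intercept variance 0.6-0.5, slope variance 0-0.05.

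With group-by-time terms, random intercept and slope, and complete data within each arm, the fitted slope equals the least-squares slope of the visit means.

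**Time coded by assessment number (0, 1, 2, 3).**

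- App, four visits: (0.15 - 0.30 - 0.90)/5 = -0.21. Wait-list, three visits: -0.2/2 = -0.10. Difference: -0.11.
- Shared visits only: -0.30 - (-0.10) = -0.20.
- Fitted week-6 values: app -0.375 - 0.21 × 0.5 = -0.48; wait-list -0.20. Difference 0.28 SD, against a true 0.40.
- Other values of the app mean at time 4: -0.3 gives -0.12 + 0.10 = -0.02; -0.75 gives -0.255 + 0.10 = -0.155; -0.9 gives -0.30 + 0.10 = -0.20 (no loss).

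**Time coded in weeks (0, 3, 6, 19; mean 7, sum of squares 210).**

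- App, four visits: (1.2 + 0.6 - 7.2)/210 = -0.0257. Wait-list: -0.2/6 = -0.0333. Difference: +0.008 per week.
- Shared visits only: -0.6/6 + 0.2/6 = -0.067 per week.
- App time-4 values of -0.3 and -0.9 give +0.025 and -0.010.

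**Power, assessment coding, two-sided 5%.** The variance of one person's slope is slope variance + residual variance/Sxx, with Sxx = 5 for four visits and 2 for three.

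| Contrast | Least favourable (residual 0.5, slope 0.05) | Most favourable (residual 0.4, slope 0) |
|---|---|---|
| Slopes, four app and three wait-list visits | 0.11/√((0.15+0.30)/55) = 1.22, power 23% | 0.11/√((0.08+0.20)/55) = 1.54, power 34% |
| Slopes, three shared visits | 0.20/√(2×0.30/55) = 1.91, power 48% | 0.20/√(2×0.20/55) = 2.35, power 65% |
| Change to week 6 | 0.40/√(2×1.2/55) = 1.91, power 48% | 0.40/√(2×0.8/55) = 2.35, power 65% |

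For the last row, the variance of one person's change is 2 × residual + 4 × slope variance: 1.2 and 0.8.

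**Group main effect only, no group-by-time term.** With placebo assumed at 0, -0.2, -0.4, -0.4 and a common linear time effect, generalised least squares gives app versus wait-list of about 0.15-0.19 SD on four assessments and 0.16-0.20 SD on the shared visits. With no slope variance the shared-visit figure is simply the average over visits, (0 + 0.2 + 0.4)/3 = 0.20. The visit mismatch changes little here. But including baseline roughly halves the 0.40 SD week-6 difference, and power is about 15-25%.

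**The case against.** The strongest reply is that the harmful analysis is not written down. As worded, the slope is a random effect, the only fixed effects named are for group, and the sentence defining the main analysis speaks of the level of symptoms. The sample size uses a between-groups test, which also points to level. On that reading the mismatch has little effect. A mixed model accepts unequal numbers of visits, and time coding is often left to an analysis plan. The means and variances above are assumed, and continued improvement after week 6 would remove the loss under assessment coding.

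Most of this stands. A reader might infer that the plan tests a slope contrast, or that the app would appear worse than waiting. The document supports neither. No group-by-time term is stated, and the sign changes only with time in weeks and certain assumed follow-up values. A reader might also infer that the trial's central question is compromised. It is not: Objectives and Discussion define the aim as app versus placebo, and both of those arms have all four assessments.

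What does not stand is that this is only missing detail. The article itself fixes four assessments and a three-arm main comparison in one model, and speaks of improvement between groups. Those statements do not fit the wait-list schedule, and the text does not say which contrast resolves the conflict.

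**Conclusion.** The point holds in a conditional form. The four-assessment model and the wait-list's three-assessment schedule do not match, and the tested contrast is left open between slope and level. If slopes are compared and app users plateau after week 6, the app-versus-wait-list difference shrinks from -0.20 to -0.11 per assessment under the assumed means, and to about zero with time in weeks. The loss ranges from none to nearly complete under assessment coding, depending on the app arm's follow-up mean. If only a group main effect is tested, the mismatch itself is minor.

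Under the same assumptions, a week-6 contrast (0.40 SD, power 48-65%) does better than either reading of the current text. This should be fixed, because the wait-list is in the main analysis and the remedy is cheap. It is not a threat to the app-versus-placebo aim.

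**What to change.** In Statistical methods, state the following:

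- Visit enters as a category, with group-by-visit terms.
- Comparisons with the wait-list use baseline, week 3 and week 6 only, and the contrast is the week-6 difference.
- The 3-month follow-up is compared for app versus placebo only.
- No wait-list value is imputed or carried forward to time 4.

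This needs no new data or visits. The cost is a few more parameters than a linear slope and a plain statement that there is no untreated comparison at 3 months, which is already so by design. Under the assumed means and variances, the week-6 contrast has the same power as a slope restricted to the shared visits.
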